#### Key Economic Outcomes

##### Health-Related Outcomes

In the cost-effectiveness analyses, the main outcome will be response according to PHQ-ADS. In the cost-utility analysis, quality-adjusted life years (QALYs) will be the health-related outcome based on the AQoL-8D. The AQoL-8D generates patient preference–based utilities on a scale of 0 (death) to 1 (perfect health), using the time-trade-off method (93). QALY gains will be estimated by calculating the area under the curve (AUC) of linearly interpolated AQoL-8D utilities between measurement points to cover the follow-up period.

##### Cost Measures

The health-economic evaluation will be based on claims data provided by the statutory health insurance companies AOK Baden-Wuerttemberg and Bosch BKK and the German version of the Dutch cost questionnaire Trimbos Institute and Institute of Medical Technology Questionnaire for Costs Associated with Psychiatric Illness [TiC-P; (94, 95)], which was specifically adapted to the population of psychotherapy outpatients in Germany. Claims data will contain basic information on the insured persons like sex, age, and profession as well as information on costs, diagnoses, and treatments for the following areas: in- and outpatient care, rehabilitation, prescribed medication, and therapeutic appliances and remedies, as well as sickness benefits and disability pension. Each online session will be charged with 20 €. In addition, Ulm University will provide information on costs for providing the digital treatment to psychotherapists. We will use the TiC-P for collecting data on patient and family costs (e.g., out-of-pocket expenses) and productivity costs due to presenteeism (i.e., reduced efficiency while at work). Lost workdays due to presenteeism will be computed by taking into account the number of work days for which the participant reported reduced functioning weighted by the reported corresponding inefficiency score for those days (96).

#### Qualitative Semi-Structured Interviews

Qualitative semi-structured interviews will be conducted with a sub-group of psychotherapists in a focus group setting and with patients in individual interviews. Trained interviewers will explore acceptance, usage behavior, barriers, and facilitators of PSYCHOnlineTHERAPY_fix/flex_. The interview-guides will be developed theory-based after a literature review and with the involvement of experts.

A qualitative method with a theory-based approach should gain insights into the perspectives and experiences of both participant groups. Hence, interviews with psychotherapists will investigate barriers to and facilitators for the implementation of blended psychotherapy for depression and/or anxiety. The interview guide for psychotherapists will take into account the TDF (97), that aims to identify domains that influence the implementation of interventions and professionals‘behavior change.

Interviews with patients will provide insights into the participants' experience (e.g., acceptance, feasibility of intervention usage) with the Internet-based interventions which are blended with face-to-face sessions. The interview guide will take into account the Unified Theory of Acceptance and Use of Technology (UTAUT) model (98).

The sample size and composition will be planned to consider the different intervention groups and gain sufficient theoretical data saturation. Both PSYCHOnlineTHERAPY_fix_ and _−flex_ will be represented. Based on sample size guidelines (99), ~20 participants per group (PSYCHOnlineTHERAPY_fix/flex_) in each study with psychotherapists and patients are estimated to be necessary. However, final sampling follows theoretical data saturation principles (100, 101).

#### Reimbursement

Trial participants will receive the following compensations for their study related efforts:

Trial psychotherapists will receive 1.000 € for the one-day training course as compensation for their non-realized incomes, 44.80 € for each successfully recruited study patient as compensation for the time necessary to conduct the informed consent process, and 120 € for every provided complete therapy process documentation sheet per patient after completion of the treatment within the study. Additionally, psychotherapists taking part in the qualitative interview will receive 100 € as compensation for their effort and not-realized income in this time.

Trial patients will receive 20 € for completed 18 weeks (T3) and 6 months (T4) follow-up. T5 onwards are not covered by the PSYCHOnlineTHERAPY grant. Hence, compensation can only be realized in case of additional funding. Additionally, patients taking part in the qualitative interview will receive 30 € as compensation for their effort.

#### Data Management, Quality Assurance, and Safety Measures

All online assessments will be completed via LimeSurvey (installed on an internal server of the University of Erlangen-Nuernberg) and data entered will be transmitted directly and in pseudonymized form to the data-handling center at the University of Erlangen-Nuernberg. For each individual data assessment, an individualized link including the study ID of the participant is used. Participants will receive their individual links by email. For the management of participants in the therapy setting, a tablet with an integrated app is used for the therapy documentation which does not save any data but forwards them to LimeSurvey. The evaluating center will monitor the quality and completeness of the data and the compliance of the measurements with the assessment schedule determined by the study protocol.

#### Procedure on (S)AEs

Information about potential (S)AEs are obtained within diagnostic interviews, online questionnaires, and during therapy sessions. Whenever a (S)AE is detected, the incidence will be documented by either the therapist or the study personnel. During the treatment period especially the therapist is responsible for dealing with occurring (S)AEs and is informed by the study personnel about (S)AEs identified through answers of patients within the interviews or questionnaires. Critical answers within interviews are identified and documented by the interviewers who are trained in recognizing (S)AEs and provided with a detailed instruction in dealing with suicidality during interviews. Critical answers within questionnaires as defined by a score >1 on PHQ-ADS Item 9 will be forwarded to the therapist. Therapists will have to document (S)AEs and inform the study administration within 48 h on weekdays (SAEs) or within 1 week (AEs). Events occurring during the follow-up period are documented and handled by the study personnel by automatically sending information on help and emergency numbers and offering a meeting appointment via telephone for patients who give critical answers within the interviews or questionnaires. Critical answers as defined as a score >0 on PHQ-ADS Item 9 and selected items of our modified version of the Columbia-Suicide Severity Rating Scale will lead to automatic messages to patients with information on help and emergency numbers at all times of measurement. Documentations of (S)AEs will be forwarded to an independent Data Safety Monitoring Board (DSMB) which will monitor the frequency and severity of the occurring (S)AEs. Every 6 months the DSMB will be informed about documented (S)AEs and the recruitment process and if necessary can give recommendations for discontinuation or modification of the study.

### Statistical Analyses

#### Clinical Analyses

The primary outcome will be analyzed using a three-level random slope model with measurement points nested in patients and patients nested in therapists. We will include data on depression and anxiety severity assessed at four measurement points, including baseline (T0), inter-session assessments at six (T1) and 12 weeks (T2) follow-up, and post-treatment at 18 weeks post-inclusion (T3). Depression and anxiety severity will be predicted from log-transformed time (i.e., weeks since baseline), dummy-coded treatment groups, and their interactions. Random intercepts and slopes will be included to account for unexplained heterogeneity in baseline status and rate of change, both at the level of patients and therapists. The focal tests of non-inferiority will be based on the bootstrap CIs of the interactions between time and groups. All statistical analyses will be performed based on intention-to-treat (ITT) principle. Patterns of missing data will be examined and analyses will be corrected for missing data by applying multiple imputation. Additional multiple PP analyses will be conducted including only patients that provided data.

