## Abstract

**Introduction:** Internet- and mobile-based interventions (IMIs) and their integration into routine psychotherapy (i.e., blended therapy) can offer a means of complementing psychotherapy in a flexible and resource optimized way.

**Objective:** The present study will evaluate the non-inferiority, cost-effectiveness, and safety of two versions of integrated blended psychotherapy for depression and anxiety compared to standard cognitive behavioral therapy (CBT).

**Methods:** A three-armed multicenter cluster-randomized controlled non-inferiority trial will be conducted comparing two implementations of blended psychotherapy (PSYCHOnlineTHERAPY_fix/flex_) compared to CBT. Seventy-five outpatient psychotherapists with a CBT-license will be randomized in a 1:1:1 ratio. Each of them is asked to include 12 patients on average with depressive or anxiety disorders resulting in a total sample size of *N* = 900. All patients receive up to a maximum of 16 psychotherapy sessions, either as routine CBT or alternating with Online self-help sessions (fix: 8/8; flex: 0–16). Assessments will be conducted at patient study inclusion (pre-treatment) and 6, 12, 18, and 24 weeks and 12 months post-inclusion. The primary outcome is depression and anxiety severity at 18 weeks post-inclusion (post-treatment) using the Patient Health Questionnaire Anxiety and Depression Scale. Secondary outcomes are depression and anxiety remission, treatment response, health-related quality of life, patient satisfaction, working alliance, psychotherapy adherence, and patient safety. Additionally, several potential moderators and mediators including patient characteristics and attitudes toward the interventions will be examined, complemented by ecological day-to-day digital behavior variables via passive smartphone sensing as part of an integrated smart-sensing sub-study. Data-analysis will be performed on an intention-to-treat basis with additional per-protocol analyses. In addition, cost-effectiveness and cost-utility analyses will be conducted from a societal and a public health care perspective. Additionally, qualitative interviews on acceptance, feasibility, and optimization potential will be conducted and analyzed.

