### Participants and Procedure

#### Cluster Definition

The trial will be conducted in psychotherapy outpatient practices in South-West Germany (Baden-Wuerttemberg) that take part in the PNP (Psychotherapy, Neurology, Psychosomatic, and Psychiatry) selective health care services contract of the health insurance companies AOK Baden-Wuerttemberg and Bosch BKK, managed by MEDIVERBUND AG according to §73c SGB V. This contract defines (amongst others) specific psychotherapy services for patients as outlined below. Clusters are defined by psychotherapy outpatient practices that are run by licensed psychotherapists who are PNP contract partners (i.e., authorized to bill according to the PNP contract; https://www.mediverbund-ag.de/file/4922). Psychotherapists who are not PNP contract partners themselves may participate in the study, if they are employed in a practice owned by a PNP contract partner. More than one therapist per practice is allowed to participate in the study.

Psychotherapists are eligible for inclusion in case of a given informed consent and if they (a) are actively working as a psychological psychotherapist, a medical specialist for psychiatry and psychotherapy or psychosomatic medicine and psychotherapy, another physician working as psychotherapist, or a children and adolescent psychotherapist, (b) are (employed in a practice owned by) a PNP contract partner, (c) hold a CBT license, (d) are available during recruitment and assessment period (self-report regarding no already known time-offs), and (e) are capable of including 12 patients into the study during the recruitment period (18 months; self-report). Enrolment and opening of clusters will take place over the entire recruitment period in order to reach the recruitment target of 900 patients. The recruitment target is a median of 12 patients per participating psychotherapist in order to achieve recruitment of 900 patients.

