### Randomization, Allocation, and Masking

Psychotherapist outpatient practices will be consecutively randomly allocated to (a) PSYCHOnlineTHERAPY_fix_, (b) PSYCHOnlineTHERAPY_flex_, or (c) CBT_standard_ and informed about group membership via e-mail. Randomization will take place at a psychotherapist practices level. That means, therapists in joint practices are randomized jointly into one of the three trial arms to avoid trial arm contamination. Randomization will be conducted by an independent researcher who is blind regarding the study conditions. Whereas, blinding of psychotherapists is not possible, data collectors are blinded regarding treatment condition. Treatment condition is only known by the study personnel administering allocated treatments to psychotherapy practices. Randomization will be stratified by the number of therapists per practice (single therapist vs. more than one therapist). Two randomization lists will be generated by using the web-based programme Sealed Envelope (www.sealedenvelope.com). Randomization will happen on an individual level and an allocation ratio of 1:1:1 will be performed. In case of dropouts and if it becomes apparent that more than 75 therapists are needed to reach the sample size of *N* = 900 patients, additional therapists will be randomized.

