### Sample Size and Power Calculation

The sample size calculation is based on a random intercept model comparing the primary outcome (PHQ-ADS at T3) between treatment conditions while accounting for the nested structure of the data. Although this model is simpler than the target statistical analyses for the primary outcome presented below, it allows to avoid speculative assumptions about numerous unknown model parameters. The focal hypothesis is that both intervention groups PSYCHOnlineTHERAPY_fix/flex_ are not inferior to CBT_standard_ (= non-inferiority trial). Non-inferiority is assumed if the confidence interval (CI) of the standardized mean comparissson between PSYCHOnlineTHERAPY_fix/flex_ is completely above SMD = −0.24, which is considered as a lower threshold of clinical significance (49). We assume one-sided tests with α = 0.025 (Bonferroni-adjusted) and 1-ß = 0.8, an intra-cluster correlation coefficient (ICC) of 0.01 with a median cluster size of 12 eligible patients as feasible number to be recruited within the recruitment period. Based on these assumptions, the present trial aims at a sample size of 25 psychotherapy outpatient practice clusters and *n* = 300 patients per study arm with an allocation ratio of 1:1:1 (PSYCHOnlineTHERAPY_fix_, PSYCHOnlineTHERAPY_flex_, CBT_standard_; for formulas see (50).

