### Potential Problems and Solutions

In order to avoid selection bias, PSYCHOnlineTHERAPY follows strict trial role division with Ulm University as principle investigator, intervention content and IT-solution provider and interface to health care service providers and stakeholders. Evaluation of PSYCHOnlineTHERAPY takes place at University of Erlangen-Nuernberg. Thereby, the University of Erlangen-Nuernberg has established a work flow ensuring that randomization, administration of participants, and outcome assessments (interviews) will be conducted independent of each other. Particularly outcome assessors are kept blind toward trial arm allocation. At the beginning of each telephone interview, patients are asked to keep their trial arm allocation disclosed.

Trial arm contamination might occur in joint practices. Hence, psychotherapists in joint practices are randomized and allocated jointly in the same trial arm condition. Resulting clustering effects will be compensated statistically. Different to cRCTs in general practices patient-level trial arm contamination is rather unlikely, as patients do not switch psychotherapists in due course or during times of absence (e.g., vacation) of their psychotherapists. Patients will be asked whether they already took part in PSYCHOnlineTHERAPY before.

Considering that therapeutic alliance, which depends also on the characteristics of the psychotherapists, is one of the most important variables predicting the outcome of psychotherapy (119, 120), randomizing therapists runs the risk of clinically important baseline imbalance. Cluster size was optimized for the pre-specified non-inferiority margin, however, between trial arm baseline imbalance regarding therapist competency needs to be considered carefully when interpreting the final trial results.

Study and intervention protocol adherence will be improved by structured training courses, regular contacts with study psychotherapists as well as assessed via therapists' documentation of their psychotherapies.

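### Practices are randomized, but the primary model stops at therapists and its bootstrap unit is not stated, so the promised adjustment for joint practices is not delivered

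*Protocol article*

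**What the plan says.** The section Cluster Definition makes the outpatient practice the cluster and adds: "More than one therapist per practice is allowed to participate in the study". Randomization, Allocation, and Masking agrees: "Randomization will take place at a psychotherapist practices level", and "therapists in joint practices are randomized jointly into one of the three trial arms to avoid trial arm contamination". The same section stratifies by single versus multiple therapists, so joint practices are planned for.

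Clinical Analyses then specifies a "three-level random slope model with measurement points nested in patients and patients nested in therapists", with random intercepts and slopes for patients and therapists only. The non-inferiority tests rest on bootstrap intervals for the time-by-group interactions, and no resampling unit is given. Cluster bootstrapping is named only under Economic Evaluation, also without a unit. Potential Problems and Solutions says of joint practices: "Resulting clustering effects will be compensated statistically". It names no method.

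The unit is also not constant:

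- Abstract: "Seventy-five outpatient psychotherapists with a CBT-license will be randomized in a 1:1:1 ratio".
- Sample Size and Power Calculation: a "sample size of 25 psychotherapy outpatient practice clusters" and 300 patients per arm, with a cluster size of 12.
- Cluster Definition: 12 patients is the target per psychotherapist.
- Discussion, opening paragraph: 75 practices.
- Randomization, Allocation, and Masking: "Randomization will happen on an individual level and an allocation ratio of 1:1:1 will be performed".

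**The concern.** Two therapists who share a practice get their arm from one random draw. A model whose top level is the therapist treats them as two independent units. If patients or their rates of change are more alike within a practice than therapist effects explain, the standard error of the arm comparison is too small. In a non-inferiority trial this works in favour of the claim: a narrower interval clears the margin more easily.

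The sample size has a matching gap. Twelve patients is a therapist's target but is used as the size of a practice cluster. The counts of 75 therapists, 75 practices and 12 patients per cluster agree only if every practice has one therapist. With any joint practice, 75 therapists occupy fewer than 75 practices and the average cluster exceeds 12.

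**Working it through.** **Inputs from the protocol article.** Margin SMD 0.24, one-sided alpha 0.025, power 0.80, ICC 0.01, cluster size 12, 25 clusters and 300 patients per arm (Sample Size and Power Calculation). 75 therapists in total (Abstract).

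**Inputs assumed.** The share of joint practices, the number of therapists in each, the split of the ICC between practice and therapist, and an alternative ICC of 0.05. The article gives none of these.

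**Step 1, the plan's own figure.** Per arm without clustering: 2 × ((1.960 + 0.842)/0.24)² = 272.5. Design effect: 1 + (12 − 1) × 0.01 = 1.11. Product: 302.5, so 303 against 300 stated. Power at 300 per arm is Φ(0.24/√(2 × 1.11/300) − 1.960) = 0.797. The stated size is reproduced.

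**Step 2, an illustrative mix.** Take 45 single-therapist practices (12 patients each) and 15 two-therapist practices (24 each): 60 practices, 75 therapists, 900 patients.

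- Σm² = 45 × 144 + 15 × 576 = 15,120, and Σm²/Σm = 15,120/900 = 16.8.
- With the whole ICC at practice level, the design effect is 1 + (16.8 − 1) × ICC: 1.158 at ICC 0.01 and 1.79 at ICC 0.05.
- A therapist-only analysis works with 1 + 11 × ICC: 1.11 and 1.55.
- True SE over model SE is √(1.158/1.11) = 1.021 and √(1.79/1.55) = 1.075.
- Actual one-sided error is 1 − Φ(1.960/ratio): 0.0275 and 0.0341, against 0.025.
- Power with the practice as cluster at ICC 0.01 is Φ(0.24/√(2 × 1.158/300) − 1.960) = 0.780, against 0.797.

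**Step 3, other mixes.** Same formulas, 25 therapists per arm, whole ICC at practice level:

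| Joint practices, per arm | SE ratio, ICC 0.01 | One-sided error, ICC 0.01 | Power, ICC 0.01 | SE ratio, ICC 0.05 | One-sided error, ICC 0.05 |
|---|---|---|---|---|---|
| none | 1.000 | 0.025 | 0.797 | 1.000 | 0.025 |
| 6 of 25 therapists in pairs | 1.013 | 0.0265 | 0.787 | 1.045 | 0.030 |
| 12 of 25 in pairs | 1.026 | 0.028 | 0.776 | 1.089 | 0.036 |
| 24 of 25 in pairs | 1.051 | 0.031 | 0.757 | 1.171 | 0.047 |
| 24 of 25 in threes | 1.099 | 0.037 | 0.719 | 1.320 | 0.069 |

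The last two rows are extremes, shown only to bound the range. If half of the ICC sits at practice level, the third row (12 of 25 in pairs) falls to a ratio of 1.013 and an error of 0.0265 at ICC 0.01. If none does, every ratio is 1.

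**Step 4, what these figures measure.** They describe a comparison of means at 18 weeks, the simple model behind the sample size. The focal test is the time-by-group interaction in a random-slope model. Its standard error depends on how much slopes vary between therapists and practices, and the article gives no figure for that. The table is therefore a proxy for the direction and rough size.

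**The case against.** The strongest reply has four parts.

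- **The authors saw the issue.** They stratify by practice type and promise compensation. This stands: a reader might infer that practice clustering was ignored altogether, and the article does not support that. What is missing is any element of the stated analysis that carries the promise out.
- **The bootstrap could repair it.** Resampling whole practices would address the interval width, and an article may leave the unit to the statistical analysis plan. This stands as a limit: intervals that are too narrow are a risk and not an established fact. But the model's levels are fixed in the article, and an analysis plan that followed them literally would carry the gap forward.
- **The clustering may be a therapist matter.** The Discussion points to therapist characteristics as a driver of outcome. If therapists of one practice are no more alike than others, therapist nesting is correct, and in a single-therapist practice the two units coincide. This stands, so the point is conditional. Against it, the sample size section attaches its positive ICC to practice clusters.
- **The individual-level wording may be harmless.** A reader might infer that patients or single therapists are randomized. Beside the practice-level sentence and the description of consecutive allocation, it more plausibly means that practices are allocated one at a time. It needs rewording but is not evidence of a different design.

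**Conclusion.** The point holds in conditional form. The randomized unit has no place in the stated primary model, the bootstrap unit is open, and the promised compensation is therefore not delivered. Confidence intervals are too narrow only if two things are both true: practices with several participating therapists are enrolled, and outcomes or slopes correlate within practices beyond the therapist.

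At the protocol's ICC of 0.01 the effect is small: in the illustrative mix, an SE about 2% too small and one-sided error of about 2.75%. At an assumed ICC of 0.05 these become about 7% and 3.4%. Both rest on an assumed mix, on placing the whole ICC at practice level, and on the 18-week mean as a stand-in for the interaction test. A reader might infer that type I error is seriously inflated. The documents do not support this, because the larger values need a higher ICC or mostly joint practices, and neither is given. This should be corrected before analysis, but it does not invalidate the design.

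**What to change.** 1. In Clinical Analyses, state that the bootstrap behind the non-inferiority intervals resamples whole practices.
2. Add a practice-level random slope, with intercept, above the therapist where it can be estimated. The slope is the term that matters, since a practice intercept alone does little for the standard error of a time-by-group interaction. Only joint practices separate practice from therapist variance, so the model may be singular. In that case, keep the practice as the bootstrap unit.
3. In Randomization, Allocation, and Masking, replace the individual-level wording with: practice by practice within stratum.
4. Use one cluster unit in the Abstract, Cluster Definition, the randomization section, the sample size section and the Discussion, and keep 12 patients as a target per therapist.
5. Give design effect and power as a range over plausible joint-practice shares, for example power of 0.797 with none and about 0.780 for 60 practices at ICC 0.01. A single value cannot be fixed in advance, because practices may join throughout recruitment.

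The cost is slightly wider intervals, some care with model convergence, and corrected wording. No new data are needed beyond a practice identifier, which the allocation already requires.

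### The primary model subtracts baseline PHQ-ADS instead of adjusting for it and omits the randomization stratum; this gives up precision but is not an error

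*Protocol article*

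**What the plan says.** The Clinical Analyses section of the protocol article describes a three-level model. On the outcome data: "We will include data on depression and anxiety severity assessed at four measurement points, including baseline (T0", followed by weeks 6, 12 and 18. On the fixed effects: "Depression and anxiety severity will be predicted from log-transformed time (i.e., weeks since baseline), dummy-coded treatment groups, and their interactions". On the random effects: "Random intercepts and slopes will be included to account for unexplained heterogeneity in baseline status and rate of change", for patients and for therapists. On the test: "The focal tests of non-inferiority will be based on the bootstrap CIs of the interactions between time and groups". Baseline PHQ-ADS is not a covariate, and the arms are not given a common baseline mean.

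Under Randomization, Allocation, and Masking: "Randomization will be stratified by the number of therapists per practice (single therapist vs. more than one therapist"). The model has no term for this factor.

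Under Sample Size and Power Calculation, the trial is sized on T3 alone: "The sample size calculation is based on a random intercept model comparing the primary outcome (PHQ-ADS at T3) between treatment conditions". The article says that this model is simpler than the planned analysis. The margin is "SMD = −0.24, which is considered as a lower threshold of clinical significance".

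**The concern.** The group dummies give each arm a free T0 mean, so the time × group interaction compares change from baseline between arms. Subtracting baseline with a coefficient near 1 is efficient only when T0 and T3 are strongly correlated. At lower correlation it adds noise that a regression on T0 would avoid, and the confidence interval is wider than the data allow. In a non-inferiority trial a wider interval makes it harder to clear the margin. The stratification factor is known for every practice, and leaving it out forgoes whatever it explains.

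**Working it through.** **Inputs from the article.** Margin 0.24 SD; one-sided α = 0.025; power 0.80; ICC 0.01; 12 patients per cluster; 25 clusters and 300 patients per arm; visits at weeks 0, 6, 12 and 18.

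**Assumptions, because the article does not give them.** True difference 0, complete data, the T0–T3 correlation r, the covariance over time, and time coded as log(1 + week), since log 0 is undefined at T0.

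**1. The plan's own figure.**
- n = 2(1.96 + 0.84)²/0.24² = 273 per arm.
- The design effect is 1 + 11 × 0.01 = 1.11, so 273 × 1.11 = 303, or 25.3 clusters. The stated 300 reproduces.
- At 300 per arm, SE = √(2 × 1.11/300) = 0.0860 and power = Φ(0.24/0.0860 − 1.96) = 0.797.

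This is the T3-only comparison. Its variance is set to 1 below, and power at relative variance v is Φ(0.24/(0.0860√v) − 1.96).

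**2. What the planned contrast does with T0.** The time values are 0, 1.946, 2.565 and 2.944, with mean 1.864. The deviations are −1.864, 0.082, 0.701 and 1.081, with sum of squares 5.140. Multiplying each by 2.944/5.140 scales the slope difference to week 18. The weights on T0 to T3 are −1.07, +0.05, +0.40 and +0.62. They sum to zero, so baseline is subtracted in full.

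**3. Matched comparison at the same r.** Generalized least squares for the planned model (25 clusters of 12 per arm) gave the standard errors below; relative variance is (SE/0.0860)². A model with T0 as covariate and visit-specific group effects has relative variance 1 − r² at T3.

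| r | Planned, random intercept and slope: SE, variance (power) | Planned, compound symmetry: SE, variance (power) | T0 covariate, visit-specific: variance (power) |
|---|---|---|---|
| 0.3 | 0.0977, 1.29 (0.69) | 0.0887, 1.06 (0.77) | 0.91 (0.83) |
| 0.5 | 0.0829, 0.93 (0.83) | 0.0750, 0.76 (0.89) | 0.75 (0.90) |
| 0.7 | 0.0649, 0.57 (0.96) | 0.0581, 0.46 (0.985) | 0.51 (0.97) |

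Visit-specific adjustment gains clearly at low r. At high r it gains little, and under compound symmetry at 0.7 it is slightly worse, because it gives up the parametric time trend.

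**4. Keeping the log-time trend.** Over eight assumed random-slope structures with r from 0.22 to 0.65, relative variances were:
- planned model: 0.58 to 1.27 (power 0.96 to 0.70);
- T0 as covariate, log-linear group effect on T1–T3: 0.52 to 0.88 (power 0.97 to 0.84);
- T0 as covariate, visit-specific effects: 0.58 to 0.95 (power 0.96 to 0.82). The ends match 1 − 0.65² = 0.58 and 1 − 0.22² = 0.95.

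**5. The stratum.** The article gives nothing from which its effect can be computed. In a contrast whose weights sum to zero, a stratum main effect alone largely cancels, so under the planned model only a stratum × time term could matter much.

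**The case against.** A growth model with T0 among the outcomes is a standard analysis, and nothing here shows bias or an inflated type I error. That stands. The analysis plan is not shown and could add covariates. That stands for the stratum in particular, but the article itself names the predictors of the primary model, and baseline adjustment is not among them.

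A reader might infer more than the article supports in four ways.

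- **That the trial is underpowered.** The sample size assumed no gain from baseline, and the planned model reaches 0.80 at moderate or high correlation. It falls short only at low r.
- **That power is 0.72.** That is the value for a plain T3-minus-T0 comparison at r = 0.4, where the relative variance is 2(1 − 0.4) = 1.20. The article plans a four-visit model, not that comparison.
- **That the larger gain from forcing a common baseline mean is available.** Patients are recruited after their practice is allocated and their therapist knows the arm, so equal baseline means are not assured. The covariate form avoids that constraint, but it does not cure selection. If arms differ systematically at T0, the covariate model and the planned model can disagree and neither is automatically right.
- **That the protocol concedes a PHQ-ADS imbalance.** Under Potential Problems and Solutions it says that "randomizing therapists runs the risk of clinically important baseline imbalance". That passage concerns therapist competency, which a T0 score does not correct.

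The stratum is the weaker half of the point. With ICC 0.01, all between-cluster variance is about 1% of the total, and omitting the factor usually makes the interval slightly conservative.

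**Conclusion.** The point holds as a loss of precision. The planned contrast subtracts T0 in full and ignores the stratum. Adjusting for T0 with the log-time trend kept lowers the relative variance from about 0.6–1.3 to about 0.5–0.9, and raises power from about 0.70–0.96 to about 0.84–0.97. The gain is largest at low T0–T3 correlation. With visit-specific effects it is smaller and close to nil at high correlation. All of these figures rest on assumed correlations, assumed covariance structures, log(1 + week) and complete data. No size can be claimed for the stratum.

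**What to change.** In the primary analysis:

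- take T1–T3 as outcomes, with T0 PHQ-ADS and its interaction with time as covariates;
- keep the log-time trend with group and time × group;
- add practice stratum (single versus more than one therapist) and its interaction with time as fixed effects;
- base the non-inferiority interval on the model's group difference at T3, which is also the declared primary endpoint.

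Keep the planned free-intercept model as a sensitivity analysis. Patients are recruited after cluster allocation, so a difference between the two results would be informative.

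The cost is wording fixed before analysis and a few extra parameters. Completing the baseline assessment is an inclusion criterion and the stratum is known at randomization, so no extra data or patients are needed.
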